## Abstract

**Background::**

Locking plate and intramedullary nail are two commonly applied methods to fix proximal humeral fractures. There are limited randomized studies that specifically evaluate the results of proximal humeral neck fractures with three-part or four-part treated by locking plates or intramedullary nails. Our goal was to compare functional outcomes, complications, and imaging features between the two groups.

**Methods::**

This single-center, prospective, randomized controlled test will be conducted in Tengzhou Central People's Hospital. Patients with these conditions will be included: age between 55 and 80 years; are able to communicate normally and agree to participate in our study; with the radiological evidence of proximal humeral fractures with three-part or four-part; surgical treatment was performed within twenty-one days after the acute fracture. Consecutive patients with proximal humeral fractures will be stochastic to be dealt with a locking plate or a bone nail. The informed consent will be acquired in each patients. Two groups will use the same postoperative rehabilitation protocol. Clinical outcomes include Intraoperative blood loss, operation time, Constant-Murley score, Disability, Arm, Shoulder and Hand score, shoulder range of motion (such as external rotation), and postoperative complications. The significance level was defaulted as *P* < .05.

**Results::**

This study will provide a solid theoretical basis for exploring which technique is better in treatment of 3-part or 4-part proximal humeral neck fractures in elderly population.

**Trial registration::**

This study protocol was registered in Research Registry (number: researchregistry6047).

## Introduction

1

Fractures of proximal humerus mostly occur in the elderly. With the aging of population becoming more and more serious, the incidence rate has raised by nearly 3 times in recent 30 years.^[1–3]^ Especially the three-part and four-part of proximal humerus fractures in the elderly are extremely difficult to treat. There are a variety of treatments for displaced and unstable proximal humeral fractures. It is difficult for the medical community to reach a consensus on the optimal treatment of injuries.^[4–8]^

Locking plate and intramedullary nail are two commonly applied methods to fix proximal humeral fractures. With the development of science, the biological stability of steel plate and nail is equally excellent.^[9–14]^ However, although the stability of plate fixation is high, the range of operation is large, which increases the risk of ischemic necrosis. The patient's rotator cuff may be torn, and the function of the nail may be damaged. Complications such as implant impact and secondary screw perforation are well known.^[15–18]^

In current literature, there are limited randomized studies that specifically evaluate the results of proximal humeral neck fractures with three-part or four-part treated by locking plates or intramedullary nails. We thus designed a prospective, randomized controlled trial of 2 groups of patients treated with intramedullary nails and locking plates for three-part or four-part proximal humeral neck fractures in patients between 55 and 80 years. Our goal was to compare functional outcomes, complications, and imaging features between the two groups.

## Materials and methods

2

### Participants

2.1

Patients with these conditions will be included: age between 55 and 80 years; are able to communicate normally and agree to participate in our study; with the radiological evidence of proximal humeral fractures with three-part or four-part; surgical treatment was performed within 21 days after the acute fracture. The excluding criteria includes proximal humeral fractures with one-part or two-part; pathologic fractures or refractures; pseudarthrosis; open fractures; ipsilateral fracture of elbow or distal radius; existing disorders such as paraplegia, disseminated sclerosis, and other related neurological diseases; and acute fracture treated surgically over 21 days after the injury.

### Study design

2.2

This single-center, prospective, randomized controlled test will be conducted in Tengzhou Central People's Hospital. Consecutive patients with proximal humeral fractures will be stochastic to be dealt with a locking plate or an bone nail. The protocol was admitted by institutional review committee of Tengzhou Central People's Hospital, with the number SD-T-C-9403. The informed consent will be acquired in each patient. This current trial proocol was recorded in the Research Registry, with the number researchregistry6047.

### Randomization and blind

2.3

After baseline estimation and data capture, patients were stochastically divided into 2 groups by using a computer-created stochastic number table: intramedullary nail and locking plate treatment. Before the surgical operation, the circulating nurse will review the stochastic number table. Patients with even numbers were arranged to the intramedullary nail group and the patients with odd numbers were arranged to the locking plate group. The closed envelope contains the process of treatment assignments. During the whole study, all the researchers could not see the specific grouping of treatment assignments (Fig. 1).

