### Statistical analysis and sample size calculation

2.7

Continuous data are expressed as mean and standard deviation, and classified data are expressed as absolute numbers and percentages. Student *t* test was used for continuous variables in normal distribution, and Mann Whitney *U* test was used for non-normal distribution. Categoric variables were dealt applying the χ^2^ test or Fisher exact test. The total number of complications was dealt considering the number of possible circumstances. The significance level was defaulted as *P* < .05.

The sample size was calculated based on an average difference of 10% between groups with constant Murley scores adjusted for age and gender. The standard deviation was 10 points, α was 5%, and the power was 80%. The sample size of 25 patients was required for each study group. To compensate for potential withdrawal during the follow-up period, each group included at least 32 patients.

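### A number table read by theatre staff under a known even/odd rule leaves concealment unsecured, and on its natural reading ensures neither 32 per group nor a balanced fracture mix

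*Protocol article*

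**What the plan says.** Protocol article, section 2.3 (Randomization and blind), describes the allocation in five statements.

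- Timing: "After baseline estimation and data capture", so allocation follows the baseline assessment.
- Source: "patients were stochastically divided into 2 groups by using a computer-created stochastic number table".
- Rule: "Patients with even numbers were arranged to the intramedullary nail group and the patients with odd numbers were arranged to the locking plate group".
- Who consults the table, and when: "Before the surgical operation, the circulating nurse will review the stochastic number table".
- Concealment: "The closed envelope contains the process of treatment assignments", followed by "During the whole study, all the researchers could not see the specific grouping of treatment assignments".

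The section does not say whether the table or the envelope governs. It also does not say whether the table holds independent random numbers or a shuffled list of patient numbers.

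Section 2.7 requires 25 patients per group and then says that, to allow for withdrawals, "each group included at least 32 patients". No total is given. Section 2.1 admits two grades of injury, "with the radiological evidence of proximal humeral fractures with three-part or four-part", without stating the expected split. The tests named in section 2.7 are two-group comparisons without covariates.

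**The concern.** The main question is concealment. The parity rule is simple and known, so a view of the table is a view of the assignments, including later ones if more than one entry is visible. This trial has features that would let foreknowledge matter. It runs at one centre (section 2.2), one senior surgeon does every operation (section 2.4), and surgery may take place at any time up to 21 days after injury, with later surgery an exclusion (section 2.1). If entries are taken up in order of operation, a change in the order could change who receives which implant. That would be selection bias, which no analysis reliably removes.

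The other two questions are secondary. If each patient is an independent even/odd draw, the two arms need not each contain 32 patients. In addition, the mix of three-part and four-part fractures, known before allocation, is left to chance in a trial of roughly 64.

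**Working it through.** **1. Concealment: the statements side by side**

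- If the table is the working source, the nurse reads the assignment from it and the envelope adds no protection against anyone who sees the table.
- If the envelope is the working source, the nurse needs no access to the table, and the stated review is an unnecessary exposure.
- If the envelopes were prepared from the table, the two can coexist. The table must then be locked away once the envelopes are filled, and section 2.3 says instead that it is consulted before surgery.

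None of these readings yields the protection that the section claims unless something unstated is added.

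**2. The plan's own group sizes**

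Inputs from section 2.7: SD 10 points, α 5% (two-sided assumed), power 80%, difference 10%.

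n per group = 2(1.96 + 0.8416)² × SD² / difference²

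- Difference 10 points: 15.7, so 16.
- Difference 8 points (10% of an assumed mean of 80): 15.70 / 0.64 = 24.5, so 25.

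The stated 25 therefore reproduces with 8 points, which is used for the power figures below. The step from 25 to 32 matches an unstated 20% loss: 25 / 0.80 = 31.25, so 32.

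**3. Arm sizes under independent even/odd draws**

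Assumed total N = 64 (2 × 32). Size of one arm: X ~ Binomial(64, 0.5).

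| Event | Formula | Result |
|---|---|---|
| Exactly 32/32 | P(X = 32) | 9.9% |
| Smaller arm 28 or fewer | 2 P(X ≤ 28) | 38.2% |
| Smaller arm below 25, before any loss | 2 P(X ≤ 24) | 6.0% |
| Expected smaller arm | E[min(X, 64 − X)] | 28.8 |

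If recruitment continues until both arms hold 32, the shortfall of 32 − 28.82 = 3.18 in the smaller arm needs on average 2 × 3.18 = 6.4 further patients, or 70.4 in total. Eighty patients suffice with probability 94%.

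**4. What unequal arms cost in power**

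Power = Φ(8 / (10 √(1/n₁ + 1/n₂)) − 1.96)

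| Split at entry | Before loss | After loss in the ratio 25/32 |
|---|---|---|
| 32:32 | 89.3% | 80.7% |
| 24:40 | 87.3% | 78.2% |
| Average over all splits | 88.8% | 80.1% |

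**5. Chance imbalance in fracture type**

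Assumed: 32 per arm and a four-part share p of 30-50%, with two independent Binomial(32, p) counts. A gap of at least 15 percentage points means at least 5 patients (5/32 = 15.6%). A gap of at least 20 points means at least 7 (7/32 = 21.9%).

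| p | SD of the difference, √(2p(1 − p)/32) | Gap ≥ 15 points | Gap ≥ 20 points |
|---|---|---|---|
| 30% | 11.5 points | 21.9% | 7.5% |
| 40% | 12.2 points | 25.1% | 9.6% |
| 50% | 12.5 points | 26.0% | 10.3% |

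**The case against.** Several objections have force.

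- **Envelopes are ordinarily filled from a random table.** A reader might infer that the table contradicts the envelope, or that the envelope conceals nothing. The document supports neither. It leaves the link unexplained, and it does not say that the nurse sees later entries, recruits patients or schedules surgery. It also places allocation after baseline and says that researchers could not see assignments. What remains is that the access is a stated step, and a fuller protocol would have to explain or withdraw it.
- **The figure of 32 is a minimum and no total is fixed.** A reader might infer that the trial will miss 32 per group. That does not follow, because recruitment can continue. If the table is a shuffled list of 1 to 64, parity gives exactly 32:32. That reading is not stated, and it would make the last assignments certain to anyone able to see the list.
- **Unequal arms cost little.** This stands: about 0.6 points of power on average, and about 2.5 points after loss at 24:40.
- **Simple randomisation is valid.** This stands. A chance excess of four-part fractures is covered by the type I error of the test, so to call it bias would be wrong. The document gives no outcome difference between the two fracture types, the 30-50% share is assumed, and the 15-point threshold is a choice.
- **Block and stratum details may sit in a fuller protocol.** Their absence from an article would not by itself be a point. They enter here because they belong to the same repair.
- **Small blocks carry their own risk.** One surgeon learns every assignment, so blocks of 2 would make some later assignments deducible. The proposed list therefore avoids them.

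**Conclusion.** The point holds, with concealment as its core. Section 2.3 gives theatre staff sight of the table under a known rule, claims concealment by envelope, and does not say how the two fit. Concealment is therefore not secured as written. This describes a possible route to bias; nothing in the document suggests that it has been used.

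On the natural reading, independent draws by parity, the rule does not ensure the stated minimum per group. The 9.9% and 6.0% figures rest on an assumed total of 64, and the average of about 70 patients on stopping once both arms hold 32. The consequence is an unplanned total more than a loss of power. The fracture mix is left to chance, with a gap of at least 15 points in 22-26% of trials under the assumed 30-50% share. The effect is on precision and on how convincing the comparison looks.

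The change should be made, because the concealment defect lies in a stated procedure and the remedy is cheap.

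**What to change.** Reword section 2.3 as follows.

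- An existing staff member outside recruitment and theatre generates and holds a 1:1 list, stratified by three-part/four-part fracture, in randomly varying blocks that avoid size 2 (for example 4 and 6). Block sizes are not disclosed to the clinical team.
- Each assignment goes into one sequentially numbered, opaque, sealed envelope, opened only after consent, eligibility and baseline data are recorded.
- The nurse opens the next envelope and has no access to the table. The even/odd rule is dropped.

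In section 2.7, state the planned total and adjust the Constant-Murley comparison for fracture type.

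With a largest block of 6, the arms can differ by at most 6/2 = 3 per stratum, or 6 over two strata. Reaching 32 in both arms then needs at most 64 + 6 = 70 patients, where 70 is about the average under independent draws.

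The cost is a new list, a set of envelopes and two reworded paragraphs. The downside is slight predictability near the end of a block, since the single surgeon learns each assignment; varying the block sizes limits it. If recruitment has begun, assignments already made stand and the new list applies to the remaining patients.

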### Surgical procedure

2.4

The patients will be operated under general anaesthesia. All surgical procedures will be done by the senior surgeon. For both methods, the patient is set in a beach chair position on a light transmitting table with standard armrests.

The traditional deltopectoral approach will be used in patients of locking plate group. Correct repair of the fracture site is performed under C-arm fluoroscopy, and then temporary Kirschner wire or reduction forceps is used to fix the fracture fragments. Locking plate is placed along the lateral edge of biceps groove at the proximal humerus. To prevent subacromial impact, the plate is placed 5 to 8 mm below the tip of the greater tubercle and 2 to 4 mm outside the biceps groove. The correct position of the plates and screws is identified by anteroposterior and axillary fluoroscopy.

The anterolateral approach will be used in patients of intramedullary nail group. A 4-cm-long incision will be made lateral to the acromion parallel to the Langer line. The insertion point was situated at the top of the humeral head, medial to the major tubercle, and lateral to the internodular sulcus. A Proximal Humeral Nail will be inserted without reaming after the fracture is fully reduced. The distal and proximal screws are implanted with assistance. Then the rotator cuff is restored, and the incision is sutured the absence of vacuum drainage.

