### Rehabilitation protocol

2.5

Two groups will use the same postoperative rehabilitation protocol. The outpatient physiotherapy program is arranged at 3 intervals, 10 times each time, lasting for 25 minutes a day. With the help of physiotherapists, passive protected area exercises begin on the first day after surgery. The limb was protected with sling for 4 weeks. Four to six weeks after the operation, they begin comprehensive active and active auxiliary exercise training. Intensive training began 3 months after operation. The patients are followed up at 2 weeks, 6 weeks, 12 weeks and every three months thereafter. The fracture healing and the cervical trunk angle are evaluated by radiology.

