### Postoperative outcome evaluation

2.6

Clinical outcomes include Intraoperative blood loss, operation time, Constant-Murley score (CMS), Disability, Arm, Shoulder and Hand (DASH) score, shoulder range of motion (such as external rotation), and postoperative complications. CMS is a multiple item functional scale used to assess pain, daily activities, range of motion, and shoulder strength. The range of the score is 0–100, indicating the worst and best shoulder function. DASH score is sensitive, reliable and effective in fracture patients, which is broadly applied to evaluate the postoperative outcomes of these patients. It consists of 30 questions, converted into one of 100 points. A higher score indicates greater disability. Image results will be obtained on two planes, and postoperative implant location, secondary humeral head displacement, osteonecrosis, nodule absorption, and secondary fixation failure will be evaluated. Implant malposition refers to the suboptimal implant position in postoperative imaging, without mechanical influences for shoulder function. Secondary fixation failure refers to severe loss of reduction during follow-up.

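### The statement that no researcher could see the allocation during the whole study is wrong for surgeon, theatre nurse and image readers, and unsupported for the Constant-Murley score and range of motion

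*Protocol article*

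**What the plan says.** The section Randomization and blind describes a computer-generated number table and closed envelopes, and then states: "During the whole study, all the researchers could not see the specific grouping of treatment assignments". The statement covers every researcher and the entire duration of the trial.

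The same section describes who handles the table and how it is read: "Before the surgical operation, the circulating nurse will review the stochastic number table", and "Patients with even numbers were arranged to the intramedullary nail group and the patients with odd numbers were arranged to the locking plate group".

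Surgical procedure names a single operator, "All surgical procedures will be done by the senior surgeon", and gives each arm its own approach. For the plate, "The traditional deltopectoral approach will be used in patients of locking plate group". For the nail, the approach is anterolateral: "A 4-cm-long incision will be made lateral to the acromion parallel to the Langer line".

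Outcomes are both clinical and radiological. Rehabilitation protocol says "The fracture healing and the cervical trunk angle are evaluated by radiology". Postoperative outcome evaluation says "Image results will be obtained on two planes, and postoperative implant location", and goes on to list humeral head displacement, osteonecrosis, nodule absorption and fixation failure. That section describes the CMS as covering pain, daily activities, range of motion and strength. It does not say who scores it or under what conditions.

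**The concern.** The sentence asserts a property that a comparison of two visibly different implants cannot have for everyone involved. Whoever operates knows the device, and whoever reads the films sees it.

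Two things are at stake. The first is reporting: if the sentence is carried into the trial report, readers will take detection bias as controlled for all outcomes, when for imaging it is not. The second is conduct: a plan that takes universal blinding for granted gives no reason to protect the assessments that could be protected. The CMS is the outcome used for the sample size and includes examined components. Implant malposition and secondary fixation failure are described through words of judgement (a suboptimal position, a severe loss of reduction), so knowledge of the implant can influence the reading.

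**Working it through.** The claim is not numerical, so the main check takes each role in turn and asks whether the sentence can be true for it.

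| Role | What the article says | Can the role be unaware of the arm throughout? |
|---|---|---|
| Circulating nurse | Reviews the number table before surgery; parity gives the arm (Randomization and blind) | No |
| Senior surgeon | Does every operation; plate through a deltopectoral approach, nail through an anterolateral one (Surgical procedure) | No |
| Image readers | Judge implant location, head displacement, fixation failure, healing and the recorded angle (Rehabilitation protocol; Postoperative outcome evaluation) | No; the plate or nail is on the image, and implant location cannot be judged without seeing it |
| CMS and range-of-motion assessor | Not identified; incisions lie in different places by arm | Possible with a separate assessor, covered scars and no access to films; none of these is described |
| Patient | Not addressed | Not determined by the article |

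The first three rows contradict the sentence. The fourth neither confirms nor contradicts it.

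**Illustration of the stakes.** The article states no assessor bias, so the shifts below are assumptions. The other inputs are SD 10, α 5%, and 25 per group (at least 32 with the withdrawal allowance), all from Statistical analysis and sample size calculation. A two-sided test is assumed, because sidedness is not stated.

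With no true difference and a constant scoring shift b that favours one arm, the t test has noncentrality b / (SD × √(2/n)).

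- n = 25: the standard error is 10 × √(2/25) = 2.83. For b = 2, 3, 4 the noncentrality is 0.71, 1.06, 1.41, and the chance of P < .05 is 10.7%, 18.0%, 28.3%.
- n = 32: the standard error is 10 × √(2/32) = 2.50. For b = 2, 3, 4 the noncentrality is 0.80, 1.20, 1.60, and the chance is 12.4%, 21.9%, 35.0%.

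Without a shift the rate is 5%. At a fixed shift the rate is higher with 32 than with 25 per group: more patients do not dilute a systematic error. The planned sample size plays no part in the main check and does not change.

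**The case against.** **It describes concealment.** The sentence follows directly on the closed envelope and may be meant for the allocation list, with researchers meaning evaluators and not the theatre team. One might add that a circulating nurse is not a researcher at all. The intention may well have been that. But concealment ends when the patient is assigned, whereas the sentence runs for the whole study and stands under a heading that names blinding. The contradiction also survives without the nurse, since image readers are evaluators on any reading.

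**A condensed article may leave blinding details to the full protocol.** This is right for the CMS assessor, and it limits the point. A reader might infer that the CMS and range of motion will be assessed unblinded, on a bare shoulder by someone who has seen the films. The article does not support that: it is silent on the assessor, on clothing and on access to images, and a blinded CMS assessor is feasible in this design. The objection does not help the sentence itself, which is a positive statement. No fuller document could make it true for the surgeon or the image readers.

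**The size of the bias is invented.** Both arms are active fixation, and the article declares no preference that would give a direction. This stands. The rejection rates show only what a given shift would do, and the conclusion does not depend on them.

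**Open operators and image readers are unavoidable here.** This is also true. The fault lies in claiming otherwise, not in their being unblinded.

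**Conclusion.** The blinding sentence is wrong as written. That is certain for the circulating nurse, the surgeon and anyone reading the images, so imaging outcomes and image-based complications cannot be reported as blinded. For the CMS and range of motion the claim is unsupported, not disproved: the scars differ by arm and no safeguard is described, but blinding could be achieved.

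No effect on the results can be quantified from the article. The illustrative false-positive rates, 11% to 28% at 25 per group and 12% to 35% at 32, rest on an assumed one-directional shift of 2 to 4 CMS points and should carry no weight beyond illustration. Randomisation, sample size and the planned tests are not affected by this point.

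**What to change.** Describe allocation concealment (table, envelopes, when they are opened) separately from blinding, and replace the sentence with a statement by role:

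- The surgeon, theatre staff and image readers are not blinded. Imaging outcomes and image-based complications are declared as assessed unblinded.
- CMS and range of motion are scored by existing staff who were not in theatre and do not see the films, with the scar area covered in both arms. If this cannot be arranged, these outcomes are declared unblinded as well.

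Coding the groups for the analyst, or tying some imaging judgements to the angle already recorded, would be optional. Neither corrects the sentence, and an angle criterion would not cover osteonecrosis, nodule absorption or implant malposition.

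The cost is a change of wording, some reassignment of scoring among existing staff, a cover at the clinic visit, and a less favourable but accurate blinding statement. It should be checked that the cover does not hamper the measurement of motion. The scoring arrangement helps only if it is in place before assessments begin; the wording should be corrected before any report in either case.
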